### Sample size estimation

In this study, the primary outcome, PBGP, was reported at the population level using a Bayesian hierarchical model. Given the absence of formulas for sample size calculation in this type of population design, the sample size calculation in this study referred to the simulation method based on the Bayesian hierarchical model conducted by Stunnenberg et al. [23]. Additionally, the statistical power under different sample sizes was evaluated via the Markov Chain Monte Carlo (MCMC) method. The minimum clinically important difference (MCID) is an indicator used to assess the clinical significance of changes in medical outcomes [24]. It represents the smallest change in clinical outcomes that is considered meaningful by patients, clinicians, or researchers. Referring to the study by Tian et al. [25], the MCID of PBGP in this study was defined as 0.78 mmol/L, which was determined based on a 20% difference in PBGP between patients with T2DM and those with impaired fasting glucose, i.e., 3.89 mmol/L [26]. According to previous studies, the difference in PBGP between patients with diabetes consuming white rice and pasta was 2.4 mmol/L, with a between-individual SD of 2.5 mmol/L and a within-individual SD of 1.2 mmol/L [21]. At the individual level, it was assumed that the true intervention effect of each participant followed a normal distribution; at the observation level, the within-individual variation was set to be the same. Observational data for each subject were randomly generated through simulation involving 3 intervention cycles and 5 staple foods, and a Bayesian hierarchical model was constructed based on these data.

The calculation process was implemented using JAGS 4.3.0 software. Four independent MCMC chains were set up, with each chain performing 1000 burn-in iterations to eliminate dependence on initial values, followed by 4000 sampling iterations. The convergence of the posterior distribution was ensured through diagnostics using the Gelman-Rubin statistic and autocorrelation function. The criterion for determining clinical significance was set as a threshold where the posterior probability that the population effect exceeded the MCID was >80%. Simultaneously, the type I error rate under the condition of a null effect was evaluated to ensure that the false-positive rate was controlled below the nominal level (α = 0.05). Systematic simulations revealed that when the sample size reached 14, the statistical power to detect the effect size was 86.0%, with a type I error rate of 2.0% at this point, which met the requirements of a target power of 80% and a controllable error rate.

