#### Statistical hypotheses

At the individual level, the null hypothesis is that there is no difference in PBGP responses between any 2 staple foods for each participant, and the alternative hypothesis is that such differences exist. At the population level, the null hypothesis is that there is no difference in the average effect of PBGP induced by any 2 staple foods, and the alternative hypothesis is that such differences exist.

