#### Population-level N-of-1 trial analysis

For the population-level assessment of the PPGR to different staple foods, a Bayesian generalized linear mixed regression model will be used to aggregate the results from multiple *N*-of-1 trials at the population level, incorporating both between-individual and within-individual variations. Individual regression models will be linked using a random-effects model, assuming that the individual-specific regression coefficients follow a normal distribution centered on the population’s average coefficient. Noninformative priors will be used to define the variance distribution of the parameters, ensuring the robustness of the analysis. The threshold for posterior probabilities will be set at 80%. Additionally, the posterior probability of the mean differences exceeding the MCID will be evaluated.

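### The 2.0% type I error does not extend to the population hypothesis on any 2 of 5 foods, where the same rule gives roughly 24% to 30%, and the analysis section leaves the 80% threshold unattached to the MCID

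*Protocol article*

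**What the plan says.** All references are to the protocol article.

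- **Sample size estimation, effect and SDs.** The sizing rests on one contrast: "the difference in PBGP between patients with diabetes consuming white rice and pasta was 2.4 mmol/L". The between-individual SD is 2.5 mmol/L and the within-individual SD 1.2 mmol/L. Data were simulated for 3 cycles and 5 foods, and "the MCID of PBGP in this study was defined as 0.78 mmol/L".
- **Sample size estimation, rule and result.** An effect counts as clinically significant when "the posterior probability that the population effect exceeded the MCID was >80" per cent. Type I error was evaluated under a null effect "to ensure that the false-positive rate was controlled below the nominal level (α = 0.05"). One power and one error rate are reported for 14 participants: "power to detect the effect size was 86.0%, with a type I error rate of 2.0% at this point". The contrast, direction or set of contrasts that the 2.0% refers to is not given.
- **Statistical hypotheses.** The population-level null is that "there is no difference in the average effect of PBGP induced by any 2 staple foods". The alternative is that differences exist, with no direction and no primary pair.
- **Population-level N-of-1 trial analysis.** "The threshold for posterior probabilities will be set at 80%. Additionally, the posterior probability of the mean differences exceeding the MCID will be evaluated". The individual-level section also introduces an 80% threshold without saying which probability it applies to.
- **Exploratory analysis.** The only multiplicity adjustment described is a false discovery rate correction for the microbiota work.

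**The concern.** Five foods give 10 pairs and 20 directed comparisons. An error rate found for one comparison says little about the chance that at least one of the 10 pairs is declared different when all foods are the same. The protocol offers one error rate as evidence that its requirement is met, and then states a hypothesis that any pair can overturn. A reader would take the 0.05 assurance to cover a statement that some staple foods differ on the primary outcome.

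The second gap adds to this. The design section ties 80% to the probability of exceeding the MCID. The population-level analysis states 80% with no quantity and then lists the MCID probability as a further item. An analyst could apply 80% to a probability that was never simulated.

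**Working it through.** **Inputs (Sample size estimation):** n = 14; 3 cycles; MCID 0.78; effect 2.4; between-person SD 2.5; within-person SD 1.2 (all mmol/L); rule P(effect > 0.78) > 0.80.

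**Assumptions:** normal approximation to the hierarchical model; vague priors; for the error rates, all five foods identical.

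**1. The plan's own figures, one contrast in one direction, SD 2.5 on the contrast**

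- Variance of one person's contrast = 2.5² + 2 × 1.2²/3 = 6.25 + 0.96 = 7.21
- SE = √(7.21/14) = 0.718
- The rule fires when the estimate exceeds 0.78 + 0.8416 × 0.718 = 1.384
- Power = P(Z > (1.384 − 2.4)/0.718) = 92.2%
- Type I error = P(Z > 1.384/0.718) = P(Z > 1.93) = 2.7%

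Simulation with a t-based rule gives 91.8% and 2.8%. The stated figures are 86.0% and 2.0%, so this is near but not a reproduction. No other reading tried gives both:

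| Reading of the SDs | Power | Type I error, one direction |
|---|---|---|
| 2.5 on the contrast | 92.2% | 2.7% |
| 2.5 per food (variance 12.5 + 0.96) | 79.1% | 5.1% |
| 2.5 as intercept variation only (variance 0.96) | about 100% | 0.01% |
| 2.5 on the contrast, within-person terms not averaged over cycles | 87.8% | 3.5% |

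Taken together, 86.0% and 2.0% imply SE = 2.4/(2.054 + 1.080) = 0.766 and an effective threshold near 85%. The number of simulated trials is not given. With an assumed 100 trials, Monte Carlo error would be about ±6.8 points on power and ±2.7 points on type I error, which would cover the gap.

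**2. One contrast, both directions**

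2 × 2.69% = 5.4%, already above 0.05.

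**3. Any of the 10 pairs, either direction**

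With five identical means and equal contrast variances, at least one pair fires when the range of the five standardized means exceeds √2 times the critical value. The studentized range distribution for 5 means gives:

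| Starting point | Critical z | Any-pair false-positive rate |
|---|---|---|
| Stated 2.0% is per contrast and direction | 2.054 | 24.1% |
| SD 2.5 on every contrast | 1.929 | 30.2% (simulation 30% to 32%) |
| Stated 2.0% already covers both directions of one contrast | 2.326 | 13.6% |
| SD 2.5 per food | 1.637 | 47% (simulation 47% to 49%) |
| Assumed contrast SD 2.0 | 2.152 | 19.8% |
| Assumed contrast SD 1.5 | 2.471 | 9.7% |
| Assumed contrast SD 1.0 | 2.926 | 2.8% |

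For comparison, an any-pair rate of 5% needs a critical z of about 2.73, that is, about 0.3% per directed contrast.

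**4. What a stricter threshold would do**

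With P(difference > 0.78) > 95%, the rule fires at 0.78 + 1.645 × 0.718 = 1.960. The any-pair rate falls to about 5% to 6%. Power for the 2.4 contrast falls to 73% by the normal approximation, and to 66% to 69% in t-based simulation.

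**The case against.** **The scope of the 2.0% is inferred.** The protocol does not say that it belongs to one contrast in one direction, and data for five foods were simulated. A reader might state that scope as fact, but the documents do not support going so far. It is the nearest reading by arithmetic, and the inputs reproduce neither stated figure exactly. This stands. The conclusion does not depend on it, because the rate is still 13.6% if the 2.0% covers both directions.

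**About 30% is one point in a range.** The SD of 2.5 appears in the sentence on white rice and pasta. Similar foods, such as white and germ rice, may vary less between people, and at an assumed SD of 1.0 on every contrast the any-pair rate is under 3%. This stands, so the range and its assumptions must be shown. Reading 2.5 as intercept variation only would also make the problem vanish, but power would then be about 100%, not 86.0%, and the protocol says that true intervention effects vary between participants.

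**The 80% threshold probably means the MCID rule.** A reader might infer that the analysis will use P(difference > 0) > 80%, which would give 20% per direction and about 92% over all pairs. The protocol never states that rule. Its design section and the score in Equation 2 both use the MCID. What remains is an unnamed quantity, which one line would settle.

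**Family-wise control was not promised.** Bayesian pairwise estimates need not have it, the hypothesis can be read pair by pair, and the main aim is personal response. This has force against any demand for an adjustment. It does not rescue the assurance as written, since the protocol itself invokes null hypotheses, type I error and α = 0.05. Even for one pair, the undirected alternative gives 5.4% from its inputs.

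**Conclusion.** The concern holds in a limited form. The claimed control below 0.05 does not extend to the population hypothesis on any 2 of 5 foods under the plan's own SD. With identical foods, 14 participants, vague priors and the simulated rule, the any-pair rate is about 24% (from the stated 2.0%) to 30% (SD 2.5 on every contrast). It is 13.6% or about 47% on the other readings of the stated inputs, about 10% at an assumed SD of 1.5, and about 3% at 1.0.

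Separately, the population-level analysis does not tie its 80% threshold to the rule whose properties were simulated.

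The material does not show that the sample size is wrong for the single contrast, or that one primary pair or a stricter threshold is required. Those are trade-offs for the sponsor. What must change is an assurance that reaches further than its calculation.

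**What to change.** 1. **Sample size estimation.** State which contrast and direction the 2.0% and 86.0% refer to. Rerun the existing simulation for all 10 pairs in both directions, and report the any-pair rate beside the 2.0% with the SD assumed for each pair. Do not describe any-pair claims as controlled at 0.05.
2. **Population-level N-of-1 trial analysis.** State that the 80% threshold applies to P(difference > 0.78 mmol/L), as in the sample size section.
3. **Optional, Statistical hypotheses.** Name white rice against pasta, with its direction, as the contrast to which the stated error rate applies, and report the other nine pairs as estimates with credible intervals. The direction matters, because both directions together give about 5.4%.
4. **Optional alternative.** Require 95% for any-pair claims. This brings the rate to about 5% to 6%, but power for the 2.4 mmol/L contrast drops to about 66% to 73%, below the 80% target, so 14 participants would no longer meet it.

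Items 1 and 2 cost wording and one rerun of a simulation that already exists. The price is a less favourable stated error rate. Item 3 narrows the headline claim to one pair, and item 4 costs power or participants.

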### Statistical analysis plan

#### Data management

Analysis and reporting of the study results will follow the CONSORT guidelines, specifically the extension for *N*-of-1 trials (CENT 2015) [27]. The project management department of the Beijing Academy of Science and Technology serves as an independent data monitoring committee, supervising aspects of the trial, including participant recruitment, eligibility, randomization, compliance, and other critical elements. The committee will perform regular assessments and monitoring to ensure scientific integrity and ethical compliance throughout the trial. A designated study personnel member who is not involved in the data analysis will be responsible for regularly logging into the CGM platform (Sibionics Technology Co, Ltd) to check for any potential bias and misreported data. In case of significant violations, such as participants failing to comply with the trial requirements, being uncontactable for 3 consecutive days, or discontinuing participation due to health reasons, statistical analysis at the individual level will be precluded, and these cases will be excluded from meta-analysis at the population level.

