### Study population

Participants will be recruited from communities through advertisements posted on community bulletin boards in Beijing. The inclusion criteria of the participants are as follows: *1*) age between 18 and 70 y; *2*) T2DM diagnosis by an endocrinologist for ≥3 mo; *3*) currently under lifestyle intervention alone or stable single hypoglycemic drug treatment; *4*) be able to operate a smartphone; and *5*) be able to provide written informed consent. The exclusion criteria include the following: *1*) pregnancy, breastfeeding, or plans to become pregnant; *2*) severe metabolic disorders, gastrointestinal diseases, or psychiatric conditions; *3*) use of antibiotics within the past month prior to enrollment; *4*) adherence to special dietary patterns (e.g., ketogenic diet and low-carbohydrate diet); *5*) difficulty with chewing foods; *6*) a history of allergies or intolerance to the test foods; and *7*) frequent travelers.

Participants will maintain daily medication logs, and the research team will verify adherence through telephone follow-ups. Any adjustments to medication during the trial will result in the participant’s exclusion. If the person is interested in the study, the study investigator will schedule a personal online or a face-to-face meeting to provide oral information and answer questions. Prospective participants will be informed that they have ≥24 h to consider their participation in the study. Should they choose to participate, both the participant and the study investigator will sign the written informed consent, after which the investigator will conduct the screening process. If all inclusion criteria are fulfilled, and none of the exclusion criteria are met, the person will be included in the study. Participants have the right to withdraw from the *N*-of-1 trial at any time. All instances of participant dropout or trial interruption will be documented, including the time and reason for discontinuation.

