#### Analysis of baseline data

Descriptive statistics will be used to summarize participants’ demographic characteristics. Continuous variables will be expressed as mean ± SD, whereas categorical variables will be reported as frequency and percentages. To compare baseline characteristics between participants who withdraw and those who complete the study, we will use *t* test for continuous variables and χ^2^ test for categorical variables.

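### Whole-participant exclusion after a significant violation discards valid test days from both analyses and can bias the population contrast; the hierarchical model does not need it

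*Protocol article*

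**What the plan says.** The Data management subsection of the statistical analysis plan gives examples of the violations that it treats as significant: "such as participants failing to comply with the trial requirements, being uncontactable for 3 consecutive days, or discontinuing participation due to health reasons". It then fixes the consequence: "statistical analysis at the individual level will be precluded, and these cases will be excluded from meta-analysis at the population level". It does not say how much non-compliance counts as significant.

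Study population has a separate rule: "Any adjustments to medication during the trial will result in the participant’s exclusion". It does not say whether this means leaving the trial, removal from one or both analyses, or removal of data already collected.

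Two other provisions touch on these participants. Study population states that "All instances of participant dropout or trial interruption will be documented", with time and reason. Analysis of baseline data plans tests "To compare baseline characteristics between participants who withdraw and those who complete the study". Neither returns outcome data to an estimate.

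The population-level section specifies a mixed model with person-specific coefficients drawn from a common normal distribution. The individual-level section specifies a separate non-hierarchical model per participant with noninformative priors, and the WGRS then weights by a CV for each comparator food.

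**The concern.** All the triggers occur after randomisation, and the rule removes the participant's whole record, including meals eaten as planned before the event. With 15 test days and a 3-day washout between tests, the schedule spans about 15 + 14 × 3 = 57 days, so such events are foreseeable.

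Two things are at stake. The first is information: a participant who leaves after the second cycle has completed 10 test days, and all are lost, along with that person's individual result, which is a main product of an N-of-1 trial. The second is selection. The primary outcome is a glucose peak, and health-related stopping or a medication change in T2DM may be connected with glucose response. If removal follows the size of a participant's difference between foods, the population mean contrast and the spread between participants describe a selected group.

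This is not detail left to a fuller document. The article states the rule itself.

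**Working it through.** **Inputs.** From Sample size estimation: white rice versus pasta difference 2.4 mmol/L, between-individual SD 2.5, within-individual SD 1.2, MCID 0.78, 3 cycles, 5 foods. The success criterion is a posterior probability above 80% that the effect exceeds the MCID; at N = 14 the stated power is 86.0% and the type I error 2.0%. The article states no loss rate and no relation between loss and response, so both are assumptions below.

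**1. The plan's own power figure.** Take the between-individual SD as the SD of the person-level contrast and use a normal approximation:
- Variance of one participant's contrast over three cycles: 2.5² + 2 × 1.2²/3 = 6.25 + 0.96 = 7.21.
- SE at 14: √(7.21/14) = 0.718.
- Power: Φ((2.4 − 0.78)/0.718 − 0.842) = 92.2%. Type I error at zero effect: Φ(−0.78/0.718 − 0.842) = 2.7%.

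This does not reproduce 86.0% and 2.0%. That is not evidence of an error, because the priors, data-generating details and number of simulations are not given. Nothing below depends on the stated figure.

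**2. Information discarded.** With r completed cycles the contrast variance is 6.25 + 2.88/r.

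| Cycles completed | Variance | Information relative to three cycles | Under the stated rule |
|---|---|---|---|
| 1 | 9.13 | 7.21/9.13 = 79% | 0% |
| 2 | 7.69 | 7.21/7.69 = 94% | 0% |
| 3 | 7.21 | 100% | 0% if removed |

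The between-person term dominates, so a partly observed participant is worth nearly as much to the population contrast as a complete one.

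**3. Selection.** Suppose a fraction q is removed from the upper end of a normal propensity that has correlation ρ with the true contrast. The mean among those kept shifts by −ρ × 2.5 × φ(c)/(1 − q), where c is the (1 − q) normal quantile.
- q = 10%: φ(1.282)/0.9 = 0.195. The shift is −0.10 at ρ = 0.2 and −0.24 at ρ = 0.5.
- q = 20%: φ(0.842)/0.8 = 0.350. The shift is −0.175 at ρ = 0.2 and −0.44 at ρ = 0.5.
- ρ = 0: no shift, only lost precision.

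The range is about 0.10 to 0.44 mmol/L, or 13% to 56% of 0.78. If those removed have smaller contrasts, the sign reverses.

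The SD of the true contrast among those kept is 2.5 × √(1 − ρ²(cλ + λ²)), with λ = φ(c)/(1 − q). It falls from 2.5 to 2.49 at q = 10%, ρ = 0.2, and to 2.37 at q = 20%, ρ = 0.5.

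**4. Worst case.** Remove exactly the largest contrasts among 14. The three largest expected normal order statistics are 1.703, 1.208 and 0.901, and the SD is √7.21 = 2.685.
- Top one: −2.685 × 1.703/13 = −0.35.
- Top two: −2.685 × 2.911/12 = −0.65.
- Top three: −2.685 × 3.812/11 = −0.93.

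**5. Power under the stated criterion** (approximation of step 1, no selection).

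| Left in full | Whole removal | Leavers' one or two cycles kept |
|---|---|---|
| 14 | 92.2% | – |
| 12 | 89.4% | 91.6–92.0% |
| 11 | 87.7% | 91.4–91.9% |

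**6. Individual level.** The individual model fits five food means. One observation per food gives 5 points and 5 parameters, so no residual degrees of freedom, and no CV for any food. Two per food give 10 points and 5 residual degrees of freedom.

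**The case against.** Every participant is meant to eat all five foods, so removing a person removes all foods together. Removal driven only by overall glucose level leaves the within-person food contrast unbiased. Poor glucose control is an argument about level, and lost contact or non-compliance has no shown link to either level or contrast. This stands: selection on the contrast is a plausible risk, not a demonstrated one.

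Three stronger readings are tempting and are not supported:
- That one or two removals move the mean by close to the MCID. This needs removal of exactly the largest contrasts, and even then one removal gives 0.35/0.78 = 45%.
- That the trial has no allowance for losses. The article gives the power at 14 but never states an enrolment target, and a condensed article may leave that out.
- That a medication change removes the participant from both analyses. Study population says only exclusion, and Data management does not list medication.

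Two further points stand. Power after two or three removals stays above the 80% target in the approximation. Some minimum-data rule is also justified for individual results, because the random-effects argument does not carry over to the separate individual models.

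The documentation of dropouts and the baseline comparison may reveal selection but do not correct it. None of this gives a reason to discard valid earlier days from the population model.

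**Conclusion.** The point holds as a stated rule that works badly. It drops data that the planned hierarchical model can use, and it opens the population mean contrast and the between-person spread to selection. The discarded information follows from the article's own SDs: 79% and 94% of a full participant's contribution are set to zero.

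The bias is conditional. It is about 0.10 to 0.44 mmol/L under the assumed loss of 10–20% and correlation of 0.2–0.5, and about zero if removal relates only to overall level or to neither. The 0.35, 0.65 and 0.93 mmol/L shifts are a worst case. The power loss, from about 92% to 88–89% with 11–12 left, is secondary. The undefined threshold for a significant violation adds room for exclusion decided after the data are seen.

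**What to change.** - **Population level.** In the primary hierarchical model, include every randomised participant with all valid test days. Drop only test days affected by, or after, the violation or medication change. Keep the whole-participant exclusion as a sensitivity analysis.
- **Medication adjustment.** State that exclusion under Study population does not remove earlier valid days from this analysis.
- **Individual level.** Replace automatic preclusion with a prespecified minimum of at least two valid observations per compared food, for example two completed cycles. One per food is not enough for the individual model or the CV-weighted WGRS.
- **Definition.** Say before the data are examined what makes a violation significant and a test day valid.

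The change is to analysis-set wording only. It needs no new data and alters no clinical rule on stopping or medication. The cost is an unbalanced data set, which the population model accommodates, and less precise individual results for participants with two cycles.
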